**Fig. 2. F2:**
[figure not shown]
A timeline of experimentation over days 1–3 of the CHIPS trial.

### Transport of materials

Upon removing each HBA-CNA settle plate from their location, lids will be replaced, secured with tape and placed upright in a sterile bag. All SGGB cryovials will remain upright in a specimen transport container. All samples will be placed in an onsite refrigerator (4–8 °C) until ready for transport to the laboratory in an esky containing ice bricks, to maintain the transportation temperature below 10 °C. All samples will be transported within 8 hours of collection to the laboratory, with no samples remaining in the esky longer than 45 minutes.

### Microbiological analysis

All swabs and CNA plates collected will undergo transfer and processing for microbial culture for beta-haemolytic streptococci (BHS) using gold standard culture methodology [35] and according to Clinical and Laboratory Standards Institute (CLSI) standards. If no bacterial growth is observed after 24 hours, incubation will be extended for a further 24 hours to allow growth of slow-growing or small colonies. The presence of Strep A as indicated by β-haemolytic morphology will be confirmed with subculture, bacitracin sensitivity testing and positive group A latex agglutination reaction (Streptex, Thermo Scientific). Strep A isolates will be stored at −80 °C to permit further strain characterization. Results will be reported as the presence or absence of Strep A on each sample. Quantitation of the amount of Strep A is not possible with this experimental design.

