### Study procedures

**1. The capture of environmental Strep A in the vicinity of a potential infection**

Experiments will be completed at three timepoints: 24, 36 and 48 hours following inoculation of the participant with Strep A (the challenge, Day 1). Prior to inoculation, one removable adhesive shelf will be placed on a solid wall 2 metres above the floor in each of the participant’s inpatient cubicles. At 09 : 00 on Day 2 (24 hours post-challenge) one horse blood agar containing colistin and nalidixic acid (HBA-CNA, Pathwest, WA, Australia) selective settle plate will be placed on each shelf and another on the overbed tables of participants. HBA-CNA settle plates that allow Strep A growth and minimize the overgrowth of swarming Gram-negative bacteria will be used throughout [34]. These will remain in position for 4 hours and be removed at 13 : 00. This same process will be repeated on Day 3 (48 hours post-challenge). Settle plates will also be placed in the same positions described above whilst participants are sleeping (approximately 36 hours post-challenge). These will be placed at 22 : 00 on Day 2 (~36 hours post-challenge) and remain in place for 8 hours, before removal at 06 : 00 on Day 3.

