## Discussion

Early studies investigating the transmission of Strep A in the 1950s by Hamburger *et al*. [14, 15, 36, 37] enhanced scientific understanding of how to prevent human-to-human transmission and have been relied upon to this day – including informing the methodology of this sub-study. Notably, Hamburger and colleagues identified Strep A to have transmission potential of up to 9.5 feet (2.9 metres) in those with a symptomatic infection whilst sneezing, although very limited transmission potential was identified at any distance whilst talking [14]. The authors believe there is a benefit in contemporary replication to confirm these findings while ascertaining whether airborne or other methods of transmission may also occur. These proposed experiments capitalize on a human challenge study being conducted and provide the opportunity to increase our understanding of Strep A transmission mechanisms in the modern era.

The timing of experimentation, specifically settle plate placement and swabbing, coincides with the periods of maximal movement in the room as participants are assessed for potential symptoms of pharyngitis and have samples taken. Hence it is expected that this will be the period where transmission potential is at its highest – a study strength. While practice with HBA-CNA plates suggests exposure for no more than 4 hours at room temperature to avoid excessive contamination and degradation of the agar [38], we hypothesize that reduced movement in the room and lower room temperatures overnight will be conducive to extending exposure of these plates to 8 hours without a cover.

Lack of facilities and resources that enable strict infection control measures (such as being able to isolate participants in a single room including own bathrooms, etc.) has often been identified as a barrier to undertaking human infection/challenge studies [39]. In our study, participants are not in separate rooms but in a hospital ward-style beds, divided by curtains. One incidental benefit of our experiments would be to demonstrate whether standard infection control measures alone (without physical isolation) are adequate for prevention of Strep A transmission and thereby demonstrate the safety of similar research studies. The penicillin concentration received by the participant will need to be factored into these observations, as current practice is to deisolate those infected with Strep A after 24 hours of appropriate antimicrobial therapy.

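### The 48 h read is triggered by absence of any bacterial growth, so a culture with other flora but no visible Strep A at 24 h does not qualify for it

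*Protocol article*

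**What the plan says.** All swabs and plates are cultured for beta-haemolytic streptococci "using gold standard culture methodology [35] and according to Clinical and Laboratory Standards Institute (CLSI) standards" (Microbiological analysis). The same section then gives a reading rule: "If no bacterial growth is observed after 24 hours, incubation will be extended for a further 24 hours", and the reason for it: "to allow growth of slow-growing or small colonies". Confirmation follows: "The presence of Strep A as indicated by β-haemolytic morphology will be confirmed with subculture, bacitracin sensitivity testing", with a group A latex test. The outcome is binary: "Results will be reported as the presence or absence of Strep A on each sample". The section adds that the amount of Strep A cannot be measured.

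Three other places bear on how often other organisms will be present at 24 h:

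- **Medium (experiment 1):** "HBA-CNA settle plates that allow Strep A growth and minimize the overgrowth of swarming Gram-negative bacteria will be used throughout".
- **Overnight plates (experiment 1):** they "remain in place for 8 hours, before removal at 06 : 00 on Day 3", against 4 hours for the daytime plates.
- **Discussion:** usual practice is "exposure for no more than 4 hours at room temperature to avoid excessive contamination and degradation of the agar". The authors hypothesise that less movement and a cooler room at night will make 8 hours workable.

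**The concern.** The condition for the second 24 hours does not match its purpose. The purpose concerns the target organism: some Strep A colonies may not be visible at the first read. The condition concerns all bacteria. One colony of an unrelated organism is enough to take a culture out of the extension, although its presence says nothing about whether a slow Strep A colony is still to come.

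Two things are at stake. First, presence or absence per sample is the only outcome, so a slow colony on a mixed culture could become a false negative. Positives may be scarce already: the Discussion reports very limited spread by talking in earlier work, and notes that penicillin may reduce recovery. Second, time under observation depends on what else grew: up to 48 hours for a clean culture and 24 hours for one with other flora. Sample types with different background growth would then be read with different sensitivity.

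**Working it through.** The plan gives no figure to reproduce here. The check is a reading of the rule, followed by an illustration with assumed inputs.

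**Step 1: what the rule does to each kind of culture at 24 h, read literally.**

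| Culture at 24 h | Second read? | Consequence |
|---|---|---|
| No growth at all | Yes | Slow Strep A can be found at 48 h |
| Beta-haemolytic colonies visible, with or without other flora | Not needed | Goes to confirmation; unaffected |
| Other flora only | No | Strep A first visible at 24–48 h could be recorded as absent |

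Only the third row is a problem. Confirmation does not rescue it, because subculture and bacitracin testing are described for beta-haemolytic growth that has already been seen.

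**Step 2: is the third row likely to be occupied?** The medium is said to restrain swarming Gram-negative bacteria; no claim is made about other flora. The Discussion treats contamination of open plates as a known risk. With 20 participants, experiment 1 yields 20 × 2 positions × 3 times = 120 plates, of which 20 × 2 = 40 are exposed for 8 hours. Experiment 2 yields 20 × 3 distances × 2 times = 120 plates, each exposed for about two minutes. Experiment 3 adds swabs of handled surfaces. Some mixed cultures are therefore plausible, but no rate is given.

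**Step 3: size of the loss.** Let s be the share of Strep A-positive cultures whose Strep A is first visible between 24 and 48 h, and b the share of those that carry other growth at 24 h. Neither is in the documents; both are assumed. Relative to reading every culture at 48 h,

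loss = b × s.

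| s | b = 0.5 | b = 0.8 | b = 1.0 |
|---|---|---|---|
| 0.05 | 2.5% | 4% | 5% |
| 0.10 | 5% | 8% | 10% |
| 0.20 | 10% | 16% | 20% |
| 0.30 | 15% | 24% | 30% |

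If b = 0 or s = 0 there is no loss.

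**Step 4: which comparisons are touched.** The Statistical analysis section compares presence of Strep A by penicillin dose and by pharyngitis status. If the loss L is the same in two such groups, the observed proportions are p₁(1 − L) and p₂(1 − L). Their ratio is unchanged, and their difference shrinks by the factor 1 − L (0.84 at L = 16%). That costs information but does not favour a group. Between sample types, b may differ. With s = 0.20, b = 0.5 in one type and b = 0.8 in another, equal true positivity would be seen in the ratio 0.90 / 0.84 = 1.07.

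**The case against.** The best defence is that no bacterial growth is shorthand for no growth of the target. The preceding sentence names beta-haemolytic streptococci and points to a cited method and to CLSI standards, and this is a condensed article. The bench procedure may read all cultures at 48 h, and nowhere does the article say that mixed cultures are closed as negative at 24 h. This is a fair limit on how firmly the loss can be asserted. It does not cure the sentence: the article states a rule, and the rule as worded does not cover the cultures that its purpose requires.

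Some stronger readings are tempting, and the documents do not support them:

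- **That Strep A is missed on every plate with background flora.** Colonies visible at 24 h are still found and confirmed.
- **That the 8-hour overnight plates lose measurably more.** Starting from b = 0.8 at 4 hours, one could compute 1 − (1 − 0.8)² = 0.96 for 8 hours, and hence 0.96 × 0.2 = 19% lost. That assumes the same contamination rate by night as by day, whereas the Discussion hypothesises quieter and cooler conditions. It gives no data either way.
- **That overbed plates lose more than shelf plates.** This is conceivable, but nothing in the article shows it.
- **That the comparisons by dose or pharyngitis status are biased.** Every participant is scheduled for the same plate positions, times and distances and the same five-item swab set. Nothing shows that background flora differs by dose or case status. The three distances in experiment 2 also share the same exposure time.

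**Conclusion.** The point holds in a limited form. As worded, the trigger excludes cultures with other growth but no visible beta-haemolytic colonies at 24 h, and for those cultures it defeats its own purpose. Strep A first visible at 24–48 h on them could be recorded as absent.

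The loss is b × s with both terms unknown. The illustrations run from zero to 30%, and the true value may be small. Sensitivity may be less comparable between sample types with different background flora. No bias is shown in the planned comparisons by dose or pharyngitis status. All of this assumes that the sentence is the full reading rule; if the cited method already requires a 48 h read of mixed cultures, the fault is in the wording alone. In a pilot of up to 20 participants this is a correction worth making because it is cheap and affects the only outcome. It is not a defect that invalidates the study.

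**What to change.** Replace the trigger with: *Every plate and swab culture without presumptive Strep A (beta-haemolytic) colonies at 24 h, whatever other growth is present, is re-incubated and read again at 48 h.* In addition:

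- record for each positive whether Strep A was found at the 24 h or the 48 h read;
- record plates overgrown at 48 h as unreadable, not negative, and report their number by sample type.

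If the cited culture method already works this way, it is enough to correct the sentence to say so.

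The cost is one more read of cultures already in the laboratory, and some unreadable plates, which become missing values in a binary outcome. The change removes the loss caused by the trigger (1 − b × s becomes 1). It does not remove masking of Strep A by other flora, so recovery may still depend to some extent on background growth.

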**2. The distance that Strep A droplets move beyond a suspected infection**

These experiments will be completed at two time points: 24 hours post-challenge and 48 hours post-challenge, commencing at 09 : 00 on Days 2 and 3, respectively. Participants will be seated on their beds in front of a table draped with a sterile mat and adjusted to be the same height as their chest. The table will be exactly 30 centimetres (cm) from the chest of the participant and will hold the HBA-CNA settle plate (Fig. 1). To understand transmission during speaking, the participant will be asked to count upwards from one in a conversational tone for one minute as recorded by a stopwatch. At the conclusion of the minute, the participant will cease counting, and the plate will remain in place for an additional minute to capture any droplets that may still be falling. The experiment will be repeated in the manner described above with new plates placed at distances of 90 and 180cm [14, 28].

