**3. The environmental assessment of the confinement room via swabbing**

Following the completion of the droplet transmission experiments, environmental swabs of five items belonging to each participant will be collected. These will include one personal item as determined by the participant, the bed remote control, bedside table, water bottle/cup and intravenous (IV) stand. Flocked swabs (Conan regular flocked swab breakpoint in peel pouch sachet; Copan, Italy) selected for appropriateness of use and transport with our selected medium will be moistened with two to three drops of sterile saline and rolled over the selected object/surface in at least two different diagonal directions across a surface area of approximately 25 cm^2^. Swabs will be placed immediately in a cryovial containing 0.5 ml of skim milk, glucose, glycerol broth (SGGB) solution (PathWest Media) kept at 4–8 °C. In addition, 10 common, high-touch areas in the confinement room will be swabbed using the same methodology, selected based on observation of the room during morning vital checks. A timeline demonstrating when each experiment will occur can be seen in Fig. 2.

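### The statement that Strep A cannot be quantified is unsupported for the directly exposed agar plates, so colony counts that could be read from them go unrecorded

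*Protocol article*

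**What the plan says.** Under Microbiological analysis, the protocol article fixes one outcome for all sample types: "Results will be reported as the presence or absence of Strep A on each sample". It then adds "Quantitation of the amount of Strep A is not possible with this experimental design". It gives no reason and draws no line between agar plates and swabs. Statistical analysis carries the binary result forward, to be set against penicillin dose and diagnosed pharyngitis with chi-square statistics.

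The samples are of two kinds.

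- **Plates.** In experiment 1 one "selective settle plate will be placed on each shelf and another on the overbed tables of participants". The timing is given as "Experiments will be completed at three timepoints: 24, 36 and 48 hours following inoculation": 4 hours on each of two mornings, and overnight plates that "remain in place for 8 hours, before removal at" 06:00. In experiment 2 a plate at 30 cm is exposed during one minute of counting aloud and one further minute, and "The experiment will be repeated in the manner described above with new plates placed at distances of 90 and 180cm".
- **Swabs.** In experiment 3 about 25 cm² of surface is swabbed. "Swabs will be placed immediately in a cryovial containing 0.5 ml of skim milk, glucose, glycerol broth (SGGB) solution".

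Where no growth is seen at 24 hours, "incubation will be extended for a further 24 hours to allow growth of slow-growing or small colonies". Growth is therefore already inspected colony by colony for beta-haemolysis.

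**The concern.** For swabs the statement is easy to accept, since the binary result comes from culture of a broth sample. For experiments 1 and 2 it does not follow from the design described. The selective agar is the collecting surface, exposure times are set in advance, and what lands and grows appears as discrete colonies. Nothing in the article prevents a reader of the plate from writing down how many there are.

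The Study objectives include the distance of droplet spread and possible airborne spread, and anticipate a look at the effect of penicillin dose. Distance and dose are questions of gradient, asked in at most 20 people across five dose levels. Under the stated outcome a plate with one colony and a plate with fifty score the same. The article says that Strep A isolates will be stored and says nothing of keeping the plates, so a count not taken at reading may not be recoverable.

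**Working it through.** **The plan's own figure.** There is none to reproduce. Sample size says no formal calculation was done, and no expected colony count, significance level or power is given.

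**Number of plates affected.** Experiment 1: 2 positions × 3 exposures = 6 per participant. Experiment 2: 3 distances × 2 days = 6 per participant. Total 12 × 20 = up to 240.

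**Step 1: information kept by present/absent.** This is the Fisher information on the log mean count from the binary result, divided by that from the count. All means *m* (colonies per plate) are assumptions.

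- Poisson counts: ratio = m / (eᵐ − 1). At m = 1, 1 / 1.718 = 0.58.
- Negative binomial with dispersion k = 1: P(positive) = m / (1 + m). The binary information is m / (1 + m)² and the count information is m / (1 + m), so the ratio is 1 / (1 + m). At m = 1 this is 0.50.

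| Mean per plate | Kept, Poisson | Kept, k = 1 |
|---|---|---|
| 0.1 | 95% | 91% |
| 0.5 | 77% | 67% |
| 1 | 58% | 50% |
| 2 | 31% | 33% |
| 5 | 3% | 17% |

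Half the information is lost at a mean of about 1.26 under Poisson (about 72% of plates positive). With overdispersion (k from 0.2 to 1) that point comes at a mean of about 0.5 to 1.

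**Step 2: power.** Assumptions: 10 v 10 participants, one plate each, negative binomial k = 1, two-sided 5%. The binary comparison is the uncorrected chi-square, since chi-square is the test the plan names. Its power was computed exactly from P(positive) = m / (1 + m). The count comparison is a Mann-Whitney test, simulated.

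| Means | Plates positive | Chi-square on present/absent | Rank test on counts |
|---|---|---|---|
| 0.1 v 0.5 | 9% v 33% | 20% | about 21-22% |
| 3 v 0.5 | 75% v 33% | 45% | 64% |
| 8 v 2 | 89% v 67% | 17% | 58% |

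Fisher's exact test would make the binary analysis look worse (27% at 3 v 0.5 and 7% at 8 v 2). Part of that is its conservatism: with equal means of 5 it rejects in 0.5% of runs, against 4.2% for the rank test. The chi-square figures are therefore the fair comparison.

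**Step 3: what the document suggests about density.** The Discussion recalls that earlier work found very little spread at any distance during talking, and says that penicillin may make growth on plates less likely. Both point towards sparse plates, most clearly for the speech plates. No figure is given for the 4-hour and 8-hour settle plates.

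**The case against.** The strongest reply is that plates may be so sparse that present/absent keeps nearly everything. For the speech plates the document's own background supports this, and the first row of each table shows how little would then be lost. This stands, and it rules out a reading that a reader might otherwise adopt: that most of the information is thrown away. That holds only if plates average more than about one colony, which the document neither states nor implies.

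Two other strong readings also fail.

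- A reader might infer that a binary outcome cannot show a gradient. Proportions positive at 30, 90 and 180 cm do show one, unless nearly all or nearly none are positive. Nor would counts rescue a dose comparison with about four people per dose (20 / 5, if spread evenly).
- A reader might object that 4-hour and 8-hour plates cannot be compared: at a constant hourly rate, 20% positive at 4 hours becomes 1 − 0.8² = 36% at 8 hours. But the planned tests are against dose and diagnosis, and every participant follows the same plate schedule. The constant rate is itself doubtful, since the Discussion expects less movement and cooler rooms overnight and notes possible degradation of agar beyond 4 hours.

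It is also fair to say that a beta-haemolytic colony is not yet a confirmed Strep A colony, that the medium holds back Gram-negative growth only, and that some plates may be overgrown. These points limit what a count means. They do not make counting impossible.

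Finally, the full protocol may give a laboratory reason that a condensed article omits. That would explain the sentence, but as printed it is an unqualified claim that the described design does not bear out for plates.

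**Conclusion.** The point holds in a limited form. The claim of impossibility is plausible for swabs and unsupported for up to 240 directly exposed plates. The cost of omitting counts ranges from negligible (20% v about 21-22% power at means of 0.1 v 0.5) to substantial (45% v 64% at 3 v 0.5; 17% v 58% at 8 v 2), with the turning point near one colony per plate. These figures rest on assumed means, k = 1, a 10 v 10 split, one plate per participant and a two-sided 5% level, none of which the document gives. Because density is unknown beforehand and counts may be lost after reading, recording them is a cheap safeguard. This is an avoidable weakness in a pilot and does not invalidate the planned present/absent summary.

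**What to change.** 1. Limit the sentence on quantitation to the swabs, or state the laboratory reason why it also applies to plates.
2. Record a presumptive (beta-haemolytic) colony count on every settle and speech plate, up to a cap fixed in advance, with representative colonies confirmed as group A by the tests already planned.
3. Fix in advance how overgrown plates are scored: a top category or an uncountable category.
4. Keep present/absent as the main summary for plates and the only outcome for swabs.
5. Analyse counts as a supporting measure, with rank or permutation tests at participant level. Compare groups within the same plate position and exposure period, and do not rely on a constant-rate time offset to bring day and night plates together.

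The cost is one more field on the laboratory form and some extra confirmations on positive plates. No further samples or participants are needed. The report should say that the count is a relative, partly presumptive measure and not the amount emitted.
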